**Methods:**

We designed a RCT. Patients with stable type 2 diabetes (glycated hemoglobin < 8%) considered eligible for discharge from specialized to primary care will be included. Those with uncontrolled ischemic heart disease, severe neuropathy, and stage IV/V nephropathy will be excluded. Enrolled patients will be randomized into two groups: follow-up supported by periodic phone calls by a nurse (intervention group) plus primary care or routine primary care only (control group). The intervention group will receive regular telephone calls (every three months for one year) and will have a toll-free number to call in case of questions about disease management. The main outcome measure is a comparison of glycemic control between groups (assessed by glycated hemoglobin) at one-year follow-up.

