### Outcomes

One year after enrollment, both groups will undergo a standardized evaluation of current diabetes management, health services support, and treatment adherence. All participants will also undergo blood and urine collection for laboratory assessment.

The primary outcome will be glycemic control measured by HbA1c. The following outcomes will also be evaluated: blood pressure control evaluation (after 5 min of seated rest); lipid control; number of severe hypoglycemia episodes; antiplatelet and statin therapy; number of physician, nurse, and dietitian appointments; rate of referral to tertiary care; current satisfaction with diabetes management; emergency visits because of acute complications of diabetes; treatment adherence; new or worsening nephropathy and peripheral neuropathy; major cardiovascular events; and death.

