### Sample size

We calculated a sample of 63 participants in each treatment arm to identify a between-group difference of 1% in HbA1c after one year, considering a standard deviation of 2%, an alpha of 0.05, and a statistical power of 80%.

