### Data collection methods

Study personnel will collect baseline data with a standardized questionnaire. Blood pressure will be measured after a 5-min rest. Information about foot sensitivity, ophthalmologic evaluation, glycemic control (HbA1c, fasting glucose), renal function (creatinine, glomerular filtration rate [GFR], and albuminuria), and lipid profile will be obtained from medical records. Follow-up information will be collected with a standardized questionnaire by telephone quarterly to assess patient’s participation and minimize follow-up dropouts. After the completion of the study, the final assessment will be performed with a standardized questionnaire. The questionnaires will evaluate the following: demographic, ethnical, and education level data; drug or alcohol use; treatment of diabetes; cardiovascular history; associated co-morbidities; hospital admissions; and smoking status. Furthermore, the final questionnaire will evaluate the treatment satisfaction, emergency visits for a diabetes reason, rate of hypoglycemia, number of primary care visits to review diabetes, and rate of referrals to tertiary care. The Brief Medication Questionnaire will be used to assess adherence and comprehension of therapy on baseline and follow-up. Blood pressure, body weight, and height and foot exam will be performed and blood and urinary samples will be collected.

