### Statistical methods

Variables with normal distribution will be presented as means ± standard deviation; asymmetric variables will be presented as median and interquartile range. Categorical variables will be presented as total counts and percentages. Normal continuous variables will be compared with Student’s t-test and categorical variables will be compared with the chi-square test. No interim analysis is planned. Main outcomes will be presented both with intention-to-treat (all randomized patients) and per-protocol (patients who received at least one telephone contact) analyses. We will use Cox regression for outcome analysis.

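### Cox regression is named for outcome analysis without restriction, although the primary outcome is a continuous HbA1c at one year and the trial is sized on a difference in means

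*Protocol article*

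**What the plan says.** On the endpoint, the Outcomes section states "The primary outcome will be glycemic control measured by HbA1c", and the abstract fixes the comparison and its time: "The main outcome measure is a comparison of glycemic control between groups (assessed by glycated hemoglobin) at one-year follow-up". The assessment is a single visit: "One year after enrollment, both groups will undergo a standardized evaluation of current diabetes management", with blood and urine taken from all participants.

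Between baseline and that visit, the Data collection methods section describes telephone contact only: "Follow-up information will be collected with a standardized questionnaire by telephone quarterly". Baseline HbA1c comes from medical records. No HbA1c measurement between baseline and one year is described.

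The Sample size section plans 63 participants per arm "to identify a between-group difference of 1% in HbA1c after one year", with an SD of 2%, alpha 0.05 and 80% power.

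The Statistical methods section assigns Student's t-test to normal continuous variables and the chi-square test to categorical ones. It says that main outcomes will be presented by intention to treat and per protocol, and closes with "We will use Cox regression for outcome analysis". It does not say which method is the primary analysis of HbA1c.

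**The concern.** A Cox model needs, for each patient, an event indicator and a time to that event or to censoring. It returns a hazard ratio. The primary outcome has neither ingredient: it is a laboratory value read at a fixed visit. The 8% figure in the Eligibility criteria section is an entry limit and is nowhere made an outcome threshold.

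The Cox sentence nevertheless covers outcome analysis in general, directly follows the sentence on main outcomes, and names the only regression model in the document. Read naturally, it includes HbA1c. The section then holds two incompatible methods for the primary outcome, with no order between them: a t-test that fits the design and a Cox model that does not.

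What is at stake is which quantity the trial reports as its main result. An analyst who takes the sentence literally would first have to invent an HbA1c event, which changes the question from the one the trial was sized to answer. Leaving the choice open also weakens prespecification in an open-label trial whose outcome assessors are not blinded.

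**Working it through.** **1. Reproduce the planned sample size.** Inputs from the Sample size section: difference 1, SD 2, alpha 0.05, power 80%. Allocation is 1:1 (Randomization and participant allocation). Sidedness is not stated.

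Formula: n per arm = 2 × SD² × (z₁₋α/₂ + z₁₋β)² / difference².

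- Two-sided: 2 × 4 × (1.960 + 0.842)² / 1 = 62.8, rounded up to **63**. This matches.
- One-sided at 0.05: 50 per arm. This does not match.
- Power at 63 per arm: 80.1% by normal approximation, 79.5% by the exact noncentral t.

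The trial was therefore sized as a two-sided comparison of two means.

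**2. Ask whether the figures could support a Cox model.** They could not. The document gives no hazard ratio, event rate or number of events. For scale only, Schoenfeld's formula, events = 4 × (z₁₋α/₂ + z₁₋β)² / (ln HR)², requires 121 events for HR 0.6 and 247 for HR 0.7. Even if all 126 patients had an event, 80% power would be reached only for a hazard ratio of about 0.61 or stronger. Nothing in the protocol connects a 1% HbA1c difference to such a figure.

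**3. Set the statements side by side.**

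| Item | What the protocol gives | What a Cox model needs |
|---|---|---|
| Outcome | HbA1c, continuous | An event |
| Timing | One value at one year | A time to event or censoring |
| Target quantity | Difference in means, 1% | Hazard ratio |
| Threshold for HbA1c as outcome | None | Needed to create an event |

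**4. Hypothetical cost of forcing HbA1c into an event.** This needs two assumptions that are not in the protocol: a control mean and an outcome cut-point. Take both as 8%, with normal values, SD 2% and an intervention mean of 7%.

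- Above 8% in control: 1 − Φ(0) = 0.500.
- Above 8% in intervention: 1 − Φ(0.5) = 0.309.
- Two-proportion (chi-square) power at 63 per arm: about **59%**, against about 80% for the t-test.
- With the cut-point kept at 8% and the assumed control mean varied from 7% to 9%: about 51% to 60%.

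This loss comes from dichotomising.

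**5. Effect of the proposed analysis on N.** Adjusting for baseline HbA1c replaces the SD by 2 × √(1 − r²), where r is the correlation between baseline and 12-month HbA1c. The protocol gives no r, so a range is shown (normal approximation, 63 per arm):

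| Assumed r | Adjusted SD | Power |
|---|---|---|
| 0 | 2.00 | 80.1% |
| 0.3 | 1.91 | 83.7% |
| 0.5 | 1.73 | 90.0% |
| 0.7 | 1.43 | 97.6% |

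No increase in N is needed at any of these values.

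**The case against.** The strongest reply is that a suitable test is already there. HbA1c is continuous, the section gives normal continuous variables a t-test, and that test matches the sample size calculation. On this reading the Cox sentence was meant for death and major cardiovascular events, which the Outcomes section lists and for which a time-to-event model is natural. The Blinding section adds that the statistical analysis will be done blind, which limits choosing a method to suit one arm.

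Much of this stands. A reader might infer that the primary analysis cannot be run, or that the protocol names no valid test; the t-test sentence rules out both. A reader might also infer that most of the power is lost. That does not follow: the loss in step 4 depends on an assumed mean, an assumed cut-point and a dichotomisation that the protocol does not propose, and a fall from about 80% to about 59% would not be most of the power in any case.

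Nor can it be said that Cox regression fails for the other outcomes because their dates go unrecorded. The article says that "the final questionnaire will evaluate the treatment satisfaction, emergency visits for a diabetes reason, rate of hypoglycemia" along with visits and referrals, and that there are quarterly telephone questionnaires as well. It is silent on dates, and that detail may sit in the full protocol or the case report form.

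What the reply does not remove is the sentence itself. It is not restricted to death or cardiovascular events, which are not the primary outcome. The t-test is given as a general rule by variable type and is not named as the primary analysis. Blind analysis limits the harm of an open choice but does not settle which method comes first. This is also not detail left to a later analysis plan: the protocol makes a positive statement about the model, and that statement conflicts with its own endpoint and sample size.

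**Conclusion.** The point holds in this form: the Cox sentence is wrong as written for the primary outcome, and it leaves the primary method unclear. Cox regression cannot estimate the difference in mean HbA1c on which 63 per arm was based, and it conflicts with the t-test in the same section. The conclusion rests on the article's text alone and needs no numerical assumption.

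The sample size is sound and reproduces exactly; the endpoint and the data to be collected are not affected. No power loss is established under the protocol as it stands. The figure of about 59% only illustrates what could follow if someone dichotomised HbA1c to make the Cox model fit, with an assumed control mean and cut-point of 8%.

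**What to change.** Make two changes to the Statistical methods section.

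1. Restrict the Cox sentence to outcomes for which event dates are recorded, for example death or major cardiovascular events if these are dated.
2. Name one primary analysis: the between-arm difference in mean HbA1c (%) at 12 months with its 95% confidence interval, from a linear model with treatment arm and baseline HbA1c.

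An unadjusted t-test would also agree with the sample size. The adjusted model is preferable because baseline HbA1c is already collected and, apart from one degree of freedom, the adjustment can only hold or raise power. The choice of models for count outcomes can be left to the statistical analysis plan.

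The cost is a few lines of text, ideally settled before the 12-month data are analysed. No new data are needed, and N stays at 63 per arm.

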### Data monitoring and auditing

Due to the lack of expected harms and the nature of the intervention and outcomes, no data monitoring committee will be created. The study coordinator will perform constant auditing of data and study conduct, but no external auditing process is planned.

### Harms

There are no expected harms to study participants, except risk of data violation. The investigators will mitigate this risk by codifying participants with an identification number. Although the intervention group is expected to be more adherent to treatment, systematic differences in diabetes management are not expected.

## Discussion

Diabetes mellitus is a chronic condition associated with high mortality, reduced quality of life, and increased health cost. In particular, patients living in developing countries experience additional problems, such as poor support and limited access to healthcare services [6]. In this context, an integrated, multidisciplinary health system focused on prevention and education strategies is the key to provide adequate care to diabetic patients. Such integrated systems should focus on providing highly effective primary care, which should be able to treat the majority of diabetic patients, and refer only those with severe complications and refractory disease. Furthermore, clinical support through telemedicine interventions could strengthen primary care and enhance its quality [7].

Brazil has an excessive number of referrals and large waiting lists for referral to specialized care, with waiting times of months to years. Moreover, specialized services are unable to meet the demand for care, which leads to overloading of endocrinology clinics with unnecessary visits.

Our study aims to explore if we can improve the performance of primary care by supporting patients in the transition from specialized to primary care through the use of telehealth services. We aim to include well-controlled patients (defined as HbA1c < 8%) who no longer benefit from specialized care to glycemic treatment adjustment. We expect to answer whether a periodic, systematic intervention focused on education and adherence can improve diabetes control and whether this strategy can support management, maintaining, or improving the treatment offered in primary care. We will explore an innovative strategy to optimize the transition of care, based on a tool that has proven benefit in diabetes management. As future perspectives, if this intervention shows benefits to diabetic patients being discharged from specialized care, an economic assessment is planned to evaluate the costs of the intervention and to discuss with stakeholders the widespread implementation.

In one previous study of low-income urban adults, periodic phone calls had a superior effect on glycemic control compared to printed education material (control). After one year, a significant decrement in HbA1c was demonstrated in the intervention group (–0.23% ± 0.11% versus +0.13% ± 0.13%; *p* = 0.04), with a better effect in patients who received more calls [8]. Similar results were found in a larger sample with fewer phone calls [9]. As expected, patients with the worst baseline glycemic control had greater reductions in HbA1c.

On the other hand, a recent meta-analysis of five studies that compared phone-call intervention with usual care in patients with type 2 diabetes showed a non-significant decrement of HbA1c values in the intervention group (pooled mean difference, –0.38%; 95% confidence interval, –0.91 to 0.16) [10]. Thus, the role of periodic educational phone calls on glycemic control remains unclear, despite some evidence for improvement [11].

Despite such evidence of improved glycemic control, long-term studies are lacking. The current literature has no information about the effects of such interventions on chronic complications of diabetes, cardiovascular events, or mortality, and the majority of studies have employed follow-up periods between six months and one year. A future long-term evaluation of the aforementioned outcomes is important to analyze the effectiveness of this intervention and decide if it is indeed useful to improve primary care, considering the cost benefit.

In summary, we believe that telehealth can be a useful tool for diabetes management, facilitating patient self-management and the transition from specialized to primary care. The results of this study will help us define whether telephone nurse support should be made widely available as a tool to reduce overcrowding of specialized services.

### Trial status

This study is currently recruiting participants. The recruitment started at June 2015 and is expected to end at June 2017.

## Abbreviations

GFR: Glomerular filtration rate
HbA1c: Glycated hemoglobin
UFRGS: Universidade Federal do Rio Grande do Sul
